#### **8.7 Premature termination of the study**

Termination of the study will be considered in the case of more than 2 patients with facial nerve damage and/or severe hearing loss, as a result of surgical damage of the facial canal or posterior canal during the operation.

Depending on the results of the interim analysis, the DSMB can advise to terminate the study.

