#### **4.3 Exclusion criteria**

A potential subject who meets any of the following criteria will be excluded from participation in this study:

- Severe disability (e.g. neurological, orthopedic, cardiovascular) according to the investigator, pregnancy or serious concurrent illness that might interfere with surgery or follow-up.
- Active additional neuro-otologic disorders that may mimic MD (e.g. vestibular migraine (VM), recurrent vestibulopathy, phobic postural vertigo, vertebro-basilar TIAs, acoustic neuroma, congenital disorders, enlarged vestibular aqueduct (EVA)-like or genetic disorders (like DFNA9), cervicogenic dizziness), based on the complete clinical record.
- Previous ear surgery for MD (IT injection is not an exclusion criterion)
- Language difficulties
- Active otitis media (with or without effusion)
- Unable or unwilling to use DizzyQuest App

- Unable to undergo MRI (such as gadolinium allergy, claustrophobia, implanted non-MRI compatible device of material, BMI)
- Deafness of the contralateral ear

- Rationale inclusion and exclusion

We aim to perform surgery only on patients with an active Ménière's disease. Because both procedures involve surgery with its associated risks, we only want to perform surgery on participants who have had no benefit of conservative medical therapy and IT injection. Moreover, this will reflect the group of patients who will undergo this surgery in usual clinical practice if this trial leads to EDB being a standard procedure. Patients with prior non-ablative surgery like ESD are excluded in order to avoid any influence in the end result. Moreover, we aim to eliminate or at least minimize all factors that might interfere with follow-up. Patients with contralateral deafness are excluded because it is not clear what the effect of EDB on hearing function is.

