### 5.1 Investigational treatment

The first part of the surgical procedure is equal in the two groups. First, a canal wall-up mastoidectomy is performed: the mastoid tegmen, sigmoid sinus, and sinodural angle are identified, and the posterior bony external ear canal wall is thinned. The posterior semi-circular canal (PSCC) and the dura mater of the posterior fossa are identified. Using the prominence of the horizontal semi-circular canal, Donaldson's line is identified to approximate the position of the endolymphatic sac. The bone over the sac and the dura are thinned with diamond burrs. The sac is completely skeletonized. The infralabyrinthine dura is exposed because the main body of the sac and its lumen often lie within this area. The bone of the vestibular aqueduct operculum is dissected. The posterior fossa dura from the retrolabyrinthine bone medial to the sac around the endolymphatic duct is exposed in order to identify the duct in its superior and inferior part in continuity from the endolymphatic sac, and to create a place to insert the tips of the instrument to clip the duct. At this level, care must be taken not to traumatize the dura, which is often thin. An (open) clip is then placed around the endolymphatic duct. After this placement, but before randomisation, a CT-scan of the petrous bone is performed to assess if the clip is adequately placed around the endolymphatic duct. If the duct is identified correctly and the clip is adequately placed, randomisation takes place.

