#### - Surgical procedure in EDB group

If the patient is allocated to the EDB-group, the clip is closed. The size and numbers of clips used will be determined intraoperatively (Weck Horizon, size 'micro' to 'wide, Teleflex). The titanium clips are applied by using a clip applicator (Weck Horizon) and a McGee bending forceps (Aesculap).

Theoretically, it is possible that the endolymphatic duct cannot be identified. In that case, the endolymphatic sac is separated from the posterior canal to ensure an arrest of the flow of endolymphatic fluid between the inner ear structures and the endolymphatic sac. This is done by placing a barrier of autologous temporal fascia glued with Tisseel. This way, the same result as blockage with a clip is obtained.

In the case of tearing of the dura leading to liquor leakage, this will be treated with tisseel, fascie and novacol. The cortex is not restored. The skin is closed in a regular way.

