### **9.2 AEs, SAEs and SUSARs**

#### **9.2.1 Adverse events (AEs)**

Adverse events are defined as any undesirable experience occurring to a patient during the study, whether or not considered related to the performed (EDB/endolymphatic sac decompression) surgery. All adverse events reported spontaneously by the patient or observed by the investigator or her staff will be recorded.

As with every surgical procedure, the operation that patients undergo comes with risks. Data in a systematic review and meta-analysis regarding perioperative and anaesthetic related mortality suggest a mortality of 34 per million (Bainbridge, 2012).

The specific risks of this surgical procedure are:

- Injury to the facial nerve: according to Saliba's protocol (2015) this occurs in less than 1% of the patients.
- Injury to posterior semi-circular canal with loss of vestibular function
- Injury to the sigmoid sinus
- Hearing loss: in less than 4% of the patients, permanent hearing loss of the operated ear was reported (Saliba, protocol 2015).
- Leakage of cerebrospinal fluid (CSF). Minor leakage occurred in 10-15 %. This was solved intraoperatively by filling with muscle autograft temporalis fascia with biological glue. There

were no postoperative complications due to the leakage (Saliba's protocol 2015; Asmar 2016). It is important to note that the surgery procedure was optimized by [name]. We expect that this results in a lower rate of CSF leaks. [name] follows the dura of the posterior cranial fossa, and has good vision at the horizontal semicircular canal after visualising Donaldson's line.

- Meningitis

- According to the study performed by Saliba, 11 out of 57 patients experienced a post-operative benign paroxysmal positional vertigo (BPPV) (Saliba, 2015). In the pilot group of 66 patients operated by [name], BPPV was not reported. The difference in BPPV incidence may be due to the enhanced technique; Saliba works towards the posterior canal whilst [name] follows the dura of the posterior fossa and usual does not blue line the posterior canal.

Adverse effects due to natural course of MD are:

- worsening of hearing loss
- worsening of vertigo
- occurrence of bilateral MD
- worsening of tinnitus

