## **9.5 Data Safety Monitoring Board (DSMB)**

A Data Safety Monitoring Board (DSMB) will be established. It will be independent from the investigators and the sponsor.

Members of the DSMB:

Dr. [name] (epidemiologist, LUMC)

[name]. [name] (statistician, LUMC)

Dr. [name] (experienced clinician in the field, Radboud UMC/Groningen UMC)

The members are not in any other way involved in the trial and have therefore no conflict of interest with the sponsor of the study.

Members will review the interim analyses for the first 21 participants 6 weeks after surgery, focussing on safety of the surgical procedures.

Termination of the trial will be considered if there are more than 2 patients with facial nerve damage and/or severe hearing loss as a result of surgical damage of the facial canal or posterior canal during the operation. The trial will be stopped in case of futility, when it seems to be unlikely that there is a clinical significant effect based on the results of the interim analysis results.

The advice(s) of the DSMB will be sent to the principal investigator of the study. Should the sponsor decide not to fully implement the advice of the committee, the sponsor will send the

advice to the reviewing METC, including a note to substantiate why (part of) the advice of the committee will not be followed.

During the time when interim analysis takes place, no new participants will be included in this study.

An extensive charter for the DSMB can be found in chapter K5 'Overige documenten' of this dossier.

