### **11.4 Benefits and risks assessment, group relatedness**

Both the EDB and decompression surgery are not without its risks.

A mastoidectomy and identification of the endolymphatic duct could lead to meningitis, hearing loss, facial nerve palsy, labyrinth function loss. Meningitis and facial nerve palsy have not been reported (nor literature nor in the pilot groups operated in Antwerp by [name]). Mild hearing loss has been seen in 2 patients in our pilot. Three patients of the pilot group treated with EDB suffered drop attacks, but recovered within 8 weeks. Moreover, in three patients operated in Antwerp, postsurgical CSF leakage occurred, but successful surgical reintervention was performed the next day.

Benefits for the participants in this study are that 50% of the participants will undergo EDB surgery of which we believe (based on the previously discussed results of EDB) that it will effectively treat their vertigo attacks. Of the participants in the decompression group, an

estimated 70% will benefit from the surgery. Therefore, only 30% of the decompression group (n = 13, 15% of the total study population) will not directly benefit from participation in the study.

Furthermore, if at the end of the study these participants would still be eligible for EDB surgery and results are in favour of the EDB procedure, EDB surgery can be performed in less time with less trauma and risk, since the access to the ED through the petrous bone has already been established during the decompression operation.

Depending on the group the participant is in, 2 or 3 CT scan will be performed.

In the EDB group, one CT scan will be performed preoperatively to assess the course of the endolymphatic duct, which is helpful preoperatively in finding the duct. After placement of the clip, a CT scan is performed to assess the clip position. After deblinding, a third CT scan can be performed to assess clip position, but only if the participant still has vertigo attacks.

In the endolymphatic sac decompression group, the same preoperative CT scan will be performed. The same peroperative CT-scan is performed to assess if structures were correctly identified.

Each performed CT scan leads to exposure to ionizing radiation: approximately 2 mSv per scan. For reference: the background radiation in the Netherlands is approximately 2.5 mSv per year.

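### The only numeric termination limit (Protocol 8.7 and 9.5) leaves out severe hearing loss caused by closing the clip without canal injury

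*Protocol*

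**What the plan says.** Section 8.7 (Premature termination of the study) sets the limit at "more than 2 patients with facial nerve damage and/or severe hearing loss, as a result of surgical damage of the facial canal", and the sentence goes on to add the posterior canal. Section 9.5 (DSMB) repeats the limit for the board and again ties the event to cause: "severe hearing loss as a result of surgical damage of the facial canal or posterior canal during the operation".

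Section 5.1 describes the operation. "The first part of the surgical procedure is equal in the two groups": mastoidectomy, exposure of the sac and duct, and an open clip around the duct. Randomisation follows, and then "If the patient is allocated to the EDB-group, the clip is closed".

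On hearing, the rationale in section 4.3 excludes contralateral deafness because "it is not clear what the effect of EDB on hearing function is". Section 9.2.1 lists hearing loss among the specific surgical risks ("in less than 4% of the patients, permanent hearing loss of the operated ear was reported") without saying what caused it. The same section lists "worsening of hearing loss" as natural course of Ménière's disease. Section 11.4 reports on the earlier cases: "Mild hearing loss has been seen in 2 patients in our pilot".

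**The concern.** Injury to the facial or posterior canal is a hazard of the drilling, which both arms undergo. The clip acts on the endolymphatic duct, which is neither canal. The one numeric rule for considering termination therefore covers an operative error common to both arms. It omits a possible harm of the step under test, even though the protocol itself calls the effect of that step on hearing unclear.

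If the rule is followed exactly, three participants in the EDB arm could lose hearing severely after clip closure and the limit would not be met. It would be met only if someone attributed those losses to canal injury. Attribution is hard here, because hearing also worsens with the disease. What is at stake is irreversible harm in the operated ear, and whether the written rule prompts a review of it.

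**Working it through.** **1. Reading the clause.** The words about cause follow directly after severe hearing loss, with a comma before them in 8.7 and none in 9.5. They could be read as qualifying hearing loss alone, or hearing loss and facial nerve damage together. Hearing loss is restricted by cause on either reading.

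**2. Is this the only numeric termination limit?** The other safety provisions, side by side:

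| Provision | Number | Restricted by cause? | Consequence |
|---|---|---|---|
| 8.7 and 9.5, termination trigger | more than 2 patients | yes, canal damage | termination considered |
| 9.1, suspension duty | none | no | sponsor must suspend |
| 8.7, interim results | none | no | DSMB can advise termination |
| 9.1, adverse events | more than 5 | no; permanent hearing loss is named | ethics committee notified |
| 9.2.2, SAE reporting | none | no | report within 7 or 15 days |
| 9.5, futility | none | not a safety rule | trial stopped |

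Only the first row joins a number to termination.

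**3. Contribution of clip-related loss.** Severe loss from clip closure without canal injury adds 0 to the count, whatever its rate. The limit of more than 2 is stated without a derivation, so there is no figure of the plan to reproduce.

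**4. Illustration of size.** Inputs: 37 EDB participants (section 4.4) and an assumed rate p of severe clip-related loss. With X binomial(37, p), the chance of passing the limit if these cases counted is

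P(X > 2) = 1 − (1−p)^37 − 37·p·(1−p)^36 − 666·p²·(1−p)^35.

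At p = 0.04: 1 − 0.221 − 0.340 − 0.255 = 0.183.

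| Assumed p | Expected cases (37p) | P(more than 2 of 37) |
|---|---|---|
| 1% | 0.37 | 0.6% |
| 2% | 0.74 | 3.8% |
| 4% | 1.48 | 18% |
| 5% | 1.85 | 28% |
| 10% | 3.70 | 73% |

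The only rate in the document is the figure of under 4% in 9.2.1. That is permanent loss of any degree and any cause, so it does not estimate p. If none of the 66 earlier EDB patients (34 + 32, section 1) had severe loss, which the protocol does not state, the exact two-sided 95% upper limit would be 1 − 0.025^(1/66) = 5.4%. That rate gives 33%.

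**5. False triggers if cause no longer matters.** Let q be an assumed 12-month rate of severe natural-course loss in both arms, with n = 74. The fraction of those losses that occurs by 3 months is also assumed.

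| q | Counted for 12 months | To 3 months, half by then | To 3 months, a quarter by then |
|---|---|---|---|
| 1% | 3.8% | 0.6% | 0.1% |
| 2% | 18% | 3.8% | 0.6% |
| 4% | 57% | 18% | 3.8% |

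Each cell is P(more than 2 of 74) at the rate counted; for example, q = 2% with a quarter by 3 months is a rate of 0.5%. Surgical losses and facial nerve damage would come on top. Requiring that the loss persists would lower the figures.

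**The case against.** The strongest reply is that the gap is narrow.

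- **Other routes can halt the trial.** The suspension duty in 9.1 is mandatory and has no restriction on cause. In that respect it is stronger than a trigger under which termination is only considered. The DSMB can also advise termination on the interim results for any safety reason. This stands. A reader might infer that clip-related hearing loss is invisible, or that nothing could stop the trial because of it. The protocol does not support that. What these routes lack is a number.
- **The clause has a plausible purpose.** Hearing fluctuates and worsens in this disease, and restricting the count to surgical injury keeps progression out of it. This is a fair reason for some filter. It does not justify a filter that also removes the step under test.
- **The charter is not shown.** Section 9.5 refers to an extensive DSMB charter, which may hold further rules. The point therefore concerns only the wording of 8.7 and 9.5.
- **The rates are assumed.** Correct: no section reports severe loss from clip closure, and the only pilot losses described are mild. A reader might infer from the table that the rule would miss a real harm in 18% of trials. That would treat the whole under-4% figure as severe and clip-caused, which the protocol does not say.

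**Conclusion.** The point holds as a matter of wording. Followed as written, the only numeric termination limit does not count severe hearing loss from clip closure without canal injury, while the protocol says the effect of EDB on hearing is not clear. This is a poorly placed restriction in a design choice; the sections do not contradict each other.

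The consequence is limited, because routes without a restriction on cause remain and one of them obliges the sponsor to suspend. The size cannot be fixed from the document. The range from 0.6% to 18% of trials rests on assumed rates of 1% to 4%, and the higher values rest on rates with still less support. Nothing in the protocol shows that EDB causes severe hearing loss. The case for change is that the harm would be irreversible and the correction is small.

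**What to change.** In 8.7 and 9.5, remove the clause on canal damage. Let the trigger count facial nerve damage and any new, persistent severe hearing loss in the operated ear compared with the preoperative audiogram. The loss should be found up to and including the 3-month audiogram and confirmed as not a transient fluctuation. It should count whatever the presumed cause, clip closure included. The number (more than 2) and the consequence (termination considered) stay as they are.

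Cost: one clause in two sections. The preoperative and 3-month audiograms are already planned (8.3.1 and 8.3.3). Confirming persistence needs a repeat audiogram in the few affected participants; the planned 6-month test can serve, or an earlier extra one if a quicker answer is wanted. No by-arm reporting of later losses is proposed, since it would need DSMB reviews beyond the one scheduled on the first 21 participants.

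Two limits remain. A few natural-course losses may count, which the 3-month window and the persistence requirement keep small and which only prompt consideration. And because the interim falls 6 weeks after the 21st operation, participants operated on late in that group will not yet have had a scheduled postoperative audiogram, so the count has to continue after the interim.

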## **9. SAFETY REPORTING**

### **9.1 Temporary halt for reasons of subject safety**

In accordance to section 10, subsection 4 of the WMO, the sponsor will suspend the study if there is sufficient ground to assume that continuation of the study will jeopardise patient health or safety. The sponsor will notify the accredited METC without undue delay of a temporary halt including the reason for such an action. The study will be suspended pending a further positive decision by the accredited METC. The main investigator ([name]) will keep the participants informed.

Interim analysis will be performed after surgical treatment of 21 participants. In case of more than 5 adverse events (such as permanent hearing loss, extra hospitalisation after surgery), the METC will be notified. In a serious adverse event, the METC will be informed within the legal requirements (< 24 hour).

Substantial protocol changes will be discussed and presented for approval by METC-LDD.

### **9.2 AEs, SAEs and SUSARs**

#### **9.2.1 Adverse events (AEs)**

Adverse events are defined as any undesirable experience occurring to a patient during the study, whether or not considered related to the performed (EDB/endolymphatic sac decompression) surgery. All adverse events reported spontaneously by the patient or observed by the investigator or her staff will be recorded.

As with every surgical procedure, the operation that patients undergo comes with risks. Data in a systematic review and meta-analysis regarding perioperative and anaesthetic related mortality suggest a mortality of 34 per million (Bainbridge, 2012).

The specific risks of this surgical procedure are:

- Injury to the facial nerve: according to Saliba's protocol (2015) this occurs in less than 1% of the patients.
- Injury to posterior semi-circular canal with loss of vestibular function
- Injury to the sigmoid sinus
- Hearing loss: in less than 4% of the patients, permanent hearing loss of the operated ear was reported (Saliba, protocol 2015).
- Leakage of cerebrospinal fluid (CSF). Minor leakage occurred in 10-15 %. This was solved intraoperatively by filling with muscle autograft temporalis fascia with biological glue. There

were no postoperative complications due to the leakage (Saliba's protocol 2015; Asmar 2016). It is important to note that the surgery procedure was optimized by [name]. We expect that this results in a lower rate of CSF leaks. [name] follows the dura of the posterior cranial fossa, and has good vision at the horizontal semicircular canal after visualising Donaldson's line.

- Meningitis

- According to the study performed by Saliba, 11 out of 57 patients experienced a post-operative benign paroxysmal positional vertigo (BPPV) (Saliba, 2015). In the pilot group of 66 patients operated by [name], BPPV was not reported. The difference in BPPV incidence may be due to the enhanced technique; Saliba works towards the posterior canal whilst [name] follows the dura of the posterior fossa and usual does not blue line the posterior canal.

Adverse effects due to natural course of MD are:

- worsening of hearing loss
- worsening of vertigo
- occurrence of bilateral MD
- worsening of tinnitus

### **9.2.2 Serious adverse events (SAEs)**

A serious adverse event is any untoward medical occurrence or effect that

- results in death;
- is life threatening (at the time of the event);
- requires hospitalisation or prolongation of existing inpatients' hospitalisation;
- results in persistent or significant disability or incapacity;
- any other important medical event that did not result in any of the outcomes listed above due to medical or surgical intervention but could have been based upon appropriate judgement by the investigator.

An elective hospital admission will not be considered as a serious adverse event.

The investigator will report all SAEs to the sponsor without undue delay after obtaining knowledge of the events.

The sponsor will report the SAEs through the web portal *ToetsingOnline* to the accredited METC that approved the protocol, within 7 days of first knowledge for SAEs that result in death or are life threatening followed by a period of maximum of 8 days to complete the initial

preliminary report. All other SAEs will be reported within a period of maximum 15 days after the sponsor has first knowledge of the serious adverse events.

